## Introduction

1

Colorectal cancer (CRC) is the second leading cause of cancer‐related death worldwide, with almost 1 million deaths reported in 2020 [1]. The incidence is expected to rise to 3.2 million cases per year by 2040 [2], highlighting the need for effective screening and surveillance strategies. Colonoscopy is essential to CRC prevention, enabling early detection and removal of precancerous lesions [3, 4, 5]. Regular surveillance colonoscopy is recommended for individuals at an elevated risk for CRC, such as those with prior adenomas, CRC, or a significant family history [6, 7, 8]. However, the increasing demand for colonoscopies [9, 10] places a significant burden on healthcare resources, especially when surveillance is performed too frequently [11, 12].

Surveillance colonoscopies can account for over one‐third of all procedures [13], with guidelines recommending intervals, based on previous findings, patient age, health status and examination [6, 14]. Guidelines for surveillance are complex and differ across the world, making adherence challenging [15, 16, 17]. Studies show that up to two‐thirds of surveillance colonoscopies occur at inappropriate intervals [15, 16, 18, 19, 20, 21] either too early, increasing risks and costs [22, 23], or too late, risking cancer progression [24].

Many systems rely on a multi‐step referral process involving specialists and family physicians, which risks patient loss to follow‐up. Furthermore, few clinical practices record patient‐reported measures to determine acceptability with the surveillance process. The Southern Co‐operative Program for the Prevention of Colorectal Cancer (SCOOP), a nurse‐coordinated registry in Australia (commenced in 1999), has demonstrated improved adherence to national guidelines (from 37% to 96% [25, 26]), reduced unnecessary procedures [27] and long‐term compliance [28, 29]. However, manual data review and collection for surveillance recommendations are resource‐intensive.

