### Inclusion and Exclusion Criteria

3.2

All colonoscopies conducted at participating hospitals will be included (Table 1), regardless of indications and patient risk factors. Individuals who opt out of having their health data audited will be excluded from the study. The hospital coverage captures approximately 50% of the colonoscopies completed in South Australia, and > 80% of procedures completed in government‐run public hospitals [33].

**TABLE 1 cam471456-tbl-0001:** South Australian public hospitals implementing the integrated nurse and digital surveillance program.

Locality	Hospital network	Included hospitals
Adelaide metropolitan	Southern Adelaide Local Health Network	Flinders Medical Centre Noarlunga Health Services
	Northern Adelaide Local Health Network	Lyell McEwin Hospital Modbury Hospital
	Central Adelaide Local Health Network	The Queen Elizabeth Hospital The Royal Adelaide Hospital
Regional	Riverland Mallee Coorong Local Health Network	Riverland General Hospital
	Eyre and Far North Local Health Network	Port Lincoln Hospital

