### Automation of Surveillance Recommendations Using Computer Algorithms

3.6

Following data collation into the clinical registry, rule‐based algorithms will provide automated recommendations for colonoscopy surveillance intervals using the patient, colonoscopy and histopathology data. Factors considered within the algorithm will include the date and quality of the colonoscopy procedure, findings from the two previous colonoscopies, age, body mass index, comorbidities that are relevant to calculating the Charlson Comorbidity Index, personal and family history of a higher risk factor including CRC, past significant neoplasia, serrated polyposis or a hereditary CRC syndrome (e.g., Lynch syndrome).

Algorithms will be primarily rule‐based, using hierarchical prioritisation. The hierarchy of criteria will be classified based on Australian clinical guidelines [6], rather than unsupervised clustering, and then integrated into recommender systems. The ruleset will be frozen, version‐controlled and include explicit conflict resolution and edge‐case handling. Risk factors considered for surveillance recommendations that align with the current Australian clinical practice guidelines are provided in Table S2.

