### Outcome Parameters

3.10

All study outcomes will be compared between baseline and post‐intervention measures. The primary outcome is the proportion of automated interval recommendations for surveillance colonoscopy that match those derived from a prespecified ruleset directly based on the Australian guidelines. This ruleset serves as the gold standard for interval assignment and is explicitly programmed from the most recent national surveillance criteria. Algorithm outputs will be independently compared against this reference ruleset, with nurse recommendations serving as a secondary comparator. Validation will be conducted blinded to algorithm outputs to avoid bias, and any discrepancies between algorithm, ruleset and clinical recommendations will be adjudicated by an independent gastroenterologist panel.

Secondary outcomes include:
The timing of the scheduled colonoscopy in relation to the recommended timeframe, with ‘on‐time’ colonoscopy defined as occurring within ±6 months of the due date specified by guideline recommendations.The time taken to review the colonoscopy outcomes and communicate the prescribed surveillance interval with the patient and family physician.The prevalence of individuals lost to follow‐up.The prevalence of patients with acceptable bowel preparation quality, complete intubation and adequate withdrawal time.The incidence rate for advanced neoplasia (with hierarchical classification prioritising invasive CRC > stage 0 CRC > advanced adenoma), including CRC, adenomatous polyps or sessile serrated lesions ≥10 mm in size, with villous change, or with high‐grade dysplasia, sessile serrated lesions with any dysplasia and any traditional serrated adenoma.The incidence rate for adverse events (e.g., bleeding, perforation, hospitalisation and death).Acceptability of the intervention to patients and clinical teams.Cost‐effectiveness of the intervention.Among the secondary outcomes, those relating to colonoscopy quality metrics and timeliness are confirmatory and prespecified, whereas patient‐reported measures and thematic feedback analyses are exploratory.

Trial findings will be reported according to the CONSORT‐AI extension guidelines [42].

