### Statistical Analyses

3.12

All sites will be allowed a three‐month post‐implementation period of transition before outcome measurement. Temporal confounding will be mitigated through the use of models (e.g., interrupted time series analysis) which adjust for secular trends. Given the stepped‐wedge cluster randomised design, analyses will explicitly include fixed effects for time period and intervention status, and random effects for site (cluster) to account for ICC. With only eight clusters, we will apply the Kenward–Roger correction to adjust standard errors and *p* values are not inflated due to small number of clusters. Data analysis will be conducted using Python (3.11) and R (version 4.4.1).

The percentage of surveillance recommendations that match with Australian guidelines will be calculated from audit data, and the prevalence of individuals lost to follow‐up, prevalence of those with acceptable colonoscopy quality, and incidence rates for advanced neoplasia and adverse events will be summarised using descriptive statistics. All measures will be directly compared to each site's own baseline measures in a paired manner using McNemar's tests for proportions, Wilcoxon and Kruskal–Wallis signed‐rank tests for continuous measures and mixed‐effects Poisson regression for incidence rates. Analyses will be conducted on an intention‐to‐treat basis. A prespecified generalised linear mixed model (GLMM) with a logit link will be used for the primary binary outcome (guideline concordance) including fixed effects for time period and intervention, random intercepts for clusters and adjustment for potential confounders (e.g., age, indication and baseline quality metrics). To address the small number of clusters (*K* = 5), we specify that inference will be based on cluster‐preserving parametric bootstrap for both the intervention coefficient and marginal contrasts. Multiple comparisons across secondary outcomes will be controlled using Holm–Bonferroni correction to limit type I error. Additional sensitivity analyses will include (i) cluster‐level summaries with Kenward–Roger correction, (ii) generalised estimating equations with small‐sample corrected SEs and (iii) permutation tests at the cluster level. If national guideline text changes during the trial, an indicator for the new guideline will be included, and analyses will be repeated using both old and new mapping.

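### The on-time outcome applies one ±6-month window to every guideline interval, and the stated baseline comparison does not account for interval length, so a change in interval mix could pass for a change in timeliness

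*Protocol article*

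**What the plan says.** Section 3.10 of the protocol article lists, as a secondary outcome, the timing of colonoscopy relative to the recommended timeframe. It defines an on-time "colonoscopy defined as occurring within ±6 months of the due date specified by guideline recommendations". Among the secondary outcomes, "those relating to colonoscopy quality metrics and timeliness are confirmatory and prespecified". The same section adds that "All study outcomes will be compared between baseline and post‐intervention measures".

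Intervals differ between patients. The Introduction describes surveillance "with guidelines recommending intervals, based on previous findings, patient age, health status and examination", and Section 3.2 includes all colonoscopies "regardless of indications and patient risk factors". The article gives no interval in months or years. Section 3.6 refers to a supplementary table that is not shown: "Risk factors considered for surveillance recommendations that align with the current Australian clinical practice guidelines are provided in Table S2".

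For analysis, Section 3.12 compares each measure with the site's own baseline in a paired way, with McNemar's test where the measure is a proportion. The sentence on the primary logit model plans "adjustment for potential confounders (e.g., age, indication and baseline quality metrics"). Section 3.12 also provides for further multivariable modelling where relevant. Its subgroup and equity analyses cover age, sex, socioeconomic status, location and comorbidity. Guideline interval is named in none of these places.

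**The concern.** A window of constant width is a loose test for a short interval and a strict one for a long interval. A single on-time percentage over all intervals averages tests of unequal strictness, with weights set by how many patients of each interval come due. If those weights differ between the control and intervention phases, the percentage can move although patients are recalled just as before.

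The Introduction describes inappropriate surveillance as "either too early, increasing risks and costs", or too late. On-time return is therefore close to what the programme is meant to improve, and the outcome is confirmatory. A difference produced by interval mix would be read as an effect of the programme, or could mask one.

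**Working it through.** The plan states no rate, sample size or power for the on-time outcome, so there is no figure to reproduce.

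**Inputs.** The ±6-month window is from Section 3.10. Interval lengths of 12, 36, 60 and 120 months are assumptions. So is the spread of return times around the due date, which the article does not give.

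**Step 1: relative tolerance.** For an interval of L months this is 6/L.

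| L (months) | Window (months) | 6/L |
|---|---|---|
| 12 | 6 to 18 | 50% |
| 36 | 30 to 42 | 17% |
| 60 | 54 to 66 | 10% |
| 120 | 114 to 126 | 5% |

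**Step 2: on-time probability for fixed behaviour.** Let the timing error be normal with mean 0 and SD s. Then P(on time) = 2Φ(6/s) − 1.

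- *SD proportional to the interval.* With s = 0.20 × L, s is 2.4, 7.2, 12 and 24 months, and P = 98.8%, 59.5%, 38.3% and 19.7% at 1, 3, 5 and 10 years.
- *Same SD in months at every interval.* With s = 3, 6 or 9 months, P = 95.4%, 68.3% or 49.5%, whatever the interval.

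**Step 3: effect of a mix shift.** Move 10% of all patients from a 1-year to a 3-year interval and leave behaviour unchanged. The change in the pooled rate is 0.10 × (P at 36 months − P at 12 months).

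| Timing SD | P at 12 months | P at 36 months | Change in pooled rate |
|---|---|---|---|
| 10% of interval | 100.0% | 90.4% | −1.0 points |
| 20% of interval | 98.8% | 59.5% | −3.9 points |
| 30% of interval | 90.4% | 42.2% | −4.8 points |
| Equal in months | same | same | 0 |

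A shift towards shorter intervals has the opposite sign.

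**Step 4: could the mix differ by phase?** Section 3.8 starts one network every 6 months and gives each of the five at least 12 months of intervention. If follow-up ends when the last network reaches 12 months (an assumption), the exposures are 4 × 6 + 12 = 36, then 30, 24, 18 and 12 months.

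- A 3-year window opens at 36 − 6 = 30 months after the index colonoscopy. Only the first network has appreciable time beyond that; the second just reaches it.
- A 5-year window opens at 54 months, beyond every exposure.
- Section 3.11 describes seven 3-month periods, which is 21 months in all. On that timetable no 3-year window opens.

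Returns assigned under the programme and seen near their due date would thus be mostly short-interval. Returns in the control phase come from earlier usual care and can include any interval.

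**The case against.** The strongest reply is that the due date follows the guideline, not the interval that the programme or a clinician assigns. A changed recommendation therefore does not by itself change how a patient is scored. This stands. A reader might infer that SCOPES shifts the mix by altering recommendations, but the definition does not allow that route. The mix has to differ through case mix, period, site, length of follow-up or guideline change, and Section 3.12 already plans an indicator and dual mapping for guideline change.

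The effect is also conditional. If delay comes from waiting lists and has the same spread in months at every interval, the mix effect is exactly zero. The article has no data either way. The rollout argument weakens too if the intervention phase counts every return in the period, whoever assigned it, or if booked rather than performed dates are scored. Early returns of long-interval patients remain observable, so even the direction of any bias is not settled.

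A reader might also infer that a patient can return at twice the interval and still count as on time. That needs an interval of 6 months or less, which the article does not show; at 12 months the limit is 18/12 = 1.5 times. Nor does it say that short-interval patients are those at highest risk: intervals also depend on age, health status and the examination.

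Finally, a condensed article may leave covariate lists and strata to an analysis plan, and it nowhere says that only a pooled rate will be reported. That is fair as far as silence goes. But the article does name a test for proportions, and that test takes no covariate. The optional multivariable modelling makes no commitment on interval length.

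**Conclusion.** The concern holds in a limited, conditional form. The unequal relative tolerance follows directly from the definition. The stated comparison for this confirmatory outcome does not account for interval length. A before-after difference in the pooled on-time rate can therefore be confounded by interval mix.

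The size depends on two things that the article does not give: how timing error varies with interval, and how far the mix differs between phases. For a 10% shift between 1-year and 3-year intervals it runs from 0 points (equal error in months) to about 1 to 5 points (SD at 10–30% of the interval). These figures illustrate the mechanism and do not predict a bias in this trial.

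The documents do not support the stronger conclusion that the ±6-month window is itself an error. The weakness lies in comparing the phases on that window without regard to interval.

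**What to change.** Keep the ±6-month definition and add three commitments to the analysis of on-time colonoscopy:

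1. Report the on-time proportion by guideline-interval category in each phase.
2. Base the phase comparison on a mixed model with the time-period, intervention and cluster terms that Section 3.12 already describes, and include guideline-interval category as a covariate.
3. Give the marginal on-time rates for both phases standardised to one interval mix, fixed in advance.

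The plan should also say which returns count in the intervention phase: all returns in the period, or only those assigned under the programme. A tolerance proportional to the interval is at most an optional sensitivity analysis, since it becomes very wide at long intervals.

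The cost is plan wording and slightly more analysis. The reference ruleset in Section 3.10 already derives the guideline interval, so no new data are needed. The downside is smaller strata, with long-interval categories likely to be sparse in the intervention phase.

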### Baseline Site Assessments

3.4

The baseline efficiency of each hospital's colonoscopy surveillance process will be determined by calculating the staffing time burdens and costs for surveillance colonoscopy, as well as the appropriateness of each given surveillance interval, and time taken from colonoscopy until the patient receives communication regarding their next interval recommendation.

As per usual hospital practice, the next recommended colonoscopy surveillance interval will be provided to the patient and their family physician by the clinical team after colonoscopy. Compliance rates will be compared to the Australian guidelines for surveillance colonoscopy [6], and the time for each patient and their family physician to receive communication regarding the surveillance interval will be determined from medical records in a random selection of 10% of the total colonoscopies completed in 1 year (5% performed for surveillance and 5% for non‐surveillance indications) per hospital. Staffing time to provide the recommendations and communications will be prospectively determined for a minimum of 50 individuals undergoing surveillance colonoscopies at each hospital, with the costs calculated through consideration of time and salary rates. Clinical teams that are involved with the surveillance processes (proceduralists, nurses, administration and family physicians) will be interviewed to collect qualitative data on acceptability and limitations of current practices.

Surveys will be collected from a random selection of 100 patients per hospital before and after their surveillance colonoscopy, capturing patient demographics, assessing colonoscopy experience, quality of life and the quality of endoscopic services provided. Quality of life will be determined using the EQ‐5D‐5L validated measure [36].

Key performance indicators for the quality of endoscopic services (using recommendations provided in several consensus reports [6, 37, 38]; Table S1) will be calculated for a period of at least 6 months.

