**FIGURE 1 cam471456-fig-0001:**
[figure not shown]
A digital healthcare approach for automated colonoscopy surveillance recommendations, integrated with a nurse‐coordinated program.

Patients and family physicians will be informed of the prescribed surveillance interval and when the next surveillance colonoscopy is due, with the timing from colonoscopy until this communication recorded. Online surveys capturing the same patient‐reported measures collected at baseline will also be offered before and after surveillance colonoscopy, commencing at each hospital, 6 months after implementation of the intervention. In addition, interviews will be conducted with the clinical teams involved in the surveillance processes (proceduralists, nurses, administration and family physicians), to gauge end‐user acceptability. Measures of the key performance indicators for the quality of endoscopic services (Table S1) will be repeated at least 6 months after implementation of the intervention at each site.

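### The communication-time outcome has no single stop event or data source across the two phases, and the stated methods have no place for episodes in which no communication occurred

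*Protocol article*

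**What the plan says.** The protocol article describes this quantity in three places.

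- **Section 3.4, Baseline Site Assessments.** The opening paragraph measures "time taken from colonoscopy until the patient receives communication regarding their next interval recommendation". The next paragraph adds the family physician and names the source: "the time for each patient and their family physician to receive communication regarding the surveillance interval will be determined from medical records", in a random 10% sample of one year's colonoscopies at each hospital. The same section sets up a separate effort measure for costing: "Staffing time to provide the recommendations and communications will be prospectively determined for a minimum of 50 individuals".
- **Section 3.8, Implementation of the Digital Process** (text after Figure 1). Patients and family physicians are told the interval and the due date, "with the timing from colonoscopy until this communication recorded". No sample or record source is named.
- **Section 3.10, Outcome Parameters.** The listed outcome is "The time taken to review the colonoscopy outcomes and communicate the prescribed surveillance interval with the patient and family physician".

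On status and use, section 3.10 opens with "All study outcomes will be compared between baseline and" post-intervention measures, and says of the secondary outcomes that "those relating to colonoscopy quality metrics and timeliness are confirmatory and prespecified". Section 3.12 assigns Wilcoxon and Kruskal–Wallis tests to continuous measures and handles missing data by multiple imputation under missing at random. Section 3.1 says that the hospital audits are repeated no sooner than six months after implementation.

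**The concern.** A before-and-after comparison of a time is interpretable only if the clock starts and stops at the same events in both phases and is read from comparable records. Here the baseline text stops at receipt. The SCOPES text stops at an event that could be dispatch or receipt. The outcome list names no event, and its wording could even be taken as staff working time.

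The second issue is what happens when nobody was told. Such an episode has no time, and not because a value went unrecorded: the event did not take place. A method that needs a number for every episode must either leave it out or supply one. The Introduction gives loss to follow-up in multi-step referral as a risk of current systems, so episodes without a communication are plausible, and they may not be equally common in the two phases.

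At stake is a timeliness result that could favour SCOPES because of how dates were captured, or understate its benefit because the worst control episodes were left out.

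**Working it through.** The article gives no sample size, standard deviation, effect size or power for this outcome (section 3.11 covers only guideline concordance and EQ-5D-5L). There is no figure to reproduce, so the check sets the texts side by side.

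| Element | 3.4 (baseline) | 3.8 (SCOPES) | 3.10 (outcome list) |
|---|---|---|---|
| Start | Colonoscopy | Colonoscopy | Not stated |
| Stop | Receipt | The communication; sent or received not stated | Not stated |
| Recipients | Patient in the opening sentence; patient and family physician in the audit sentence | Patient and family physician | Patient and family physician |
| Source | Medical records, random 10% sample | Not stated | Not stated |

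**Start.** The two phase descriptions agree. The only gap is in the outcome list.

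**Recipients.** All three sections name both. None says whether the two times are reported separately or combined, for instance as the later of the two.

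**Stop and source.** These are not the same on the page. Let *D* be the true difference in time to dispatch (control minus SCOPES) and *L* the mean lag from dispatch to receipt.

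- Receipt in control, dispatch under SCOPES: observed difference = *D* + *L*. The whole lag counts as benefit.
- The same event in both phases, with the same mean lag: observed difference = *D*. The lag cancels.

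The article does not settle which case applies and gives no value for *L*.

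**Episodes with no communication.** Let *p* be the proportion of communicated episodes completed by a chosen cut-off, and *u* the share of all episodes with no communication.

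- Communicated episodes only: the rate is *p*.
- All episodes: the rate is *p* × (1 − *u*).
- With the same *p* in both phases, the communicated-only comparison shows *p* − *p* = 0. The all-episode difference (SCOPES minus control) is *p*(1 − *u*_S) − *p*(1 − *u*_C) = *p* × (*u*_C − *u*_S).

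Each percentage point by which uncommunicated episodes are more common in control thus hides *p* of a percentage point of difference. Imputation under missing at random does not recover this, because it draws times from similar episodes in which a communication did occur. If *u*_C = *u*_S and *p* is the same, nothing is hidden in the difference, although both absolute rates are overstated. The article gives neither *u*_C nor *u*_S.

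**Direction.** The stop-event problem, if present as receipt against dispatch, inflates the SCOPES benefit. The no-communication problem understates it if such episodes are more common in control. They need not cancel.

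**The case against.** A reader might infer that the two phases definitely measure different quantities. The documents do not support that. Both phase descriptions start at colonoscopy, and all three sections name patient and family physician. The section 3.8 wording refers back to patients and physicians being informed, which can mean receipt. Baseline receipt is to be read from medical records, and the article does not say which date those records hold; if it is a dispatch date, the lag may be absent from both phases. These objections stand, and they limit the point to an undefined stop event and source.

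The repeated audits are the best defence. Section 3.4 takes guideline compliance and communication time from the same record sample, so repeating that audit could yield the same measure in both phases. But section 3.1 describes the audits and patient-reported measures in terms of guideline compliance and consumer satisfaction. The only SCOPES-phase text on communication time is in section 3.8, which does not mention the audit. The defence is plausible but not written down.

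The staff-time reading of the outcome list is weak, since section 3.4 separates effort from elapsed time and section 3.10 lists cost-effectiveness on its own. A clear definition removes it anyway.

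It can also be said that handling of events that never occur belongs in the statistical analysis plan. That would answer a complaint of silence. The article, however, does state methods for continuous measures and for missing data, and those methods, followed as written, drop or impute these episodes. A worst-rank convention within a rank test would be another remedy, but none is stated.

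Finally, the confirmatory label is an inference. Section 3.10 refers to timeliness without naming this item and could mean only on-time colonoscopy. Even then, the outcome remains one of the secondary outcomes compared between phases.

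**Conclusion.** The point holds as a matter of definition and method. Start and stop events are absent from the outcome list. The stop event and data source are not aligned between the baseline and SCOPES descriptions. The stated tests and imputation have no category for an episode in which nobody was told.

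It does not establish that the phases are non-comparable. That would require dispatch to be captured in one phase and receipt in the other, which the article does not say. Bias from uncommunicated episodes likewise requires their frequency to differ between phases. Neither size can be given, because the documents contain no lag and no non-communication rate.

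This should be corrected, given that the outcome is reasonably read as part of the confirmatory timeliness group and that the correction is cheap. It does not bear on the primary outcome.

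**What to change.** Use one definition in sections 3.4, 3.8 and 3.10: calendar days from colonoscopy to one named stop event that can be obtained from the same record source in both phases. Report patient and family physician separately. State that staff minutes are a cost input and not this outcome. If the repeated audit is meant to supply the post-implementation values, say so in sections 3.1 and 3.8.

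In section 3.12, analyse the outcome as time to event in all sampled episodes. Keep an episode with no communication as not communicated at a fixed, prespecified cut-off, and do not impute a time for it.

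Settle this before baseline abstraction: if the baseline audit captures a different event from the SCOPES record, the mismatch may not be recoverable later.

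The cost is protocol and analysis-plan wording, some extra analysis work, and a result reported as a time-to-event or proportion measure in place of a simple mean or median.
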